**Figure 1. F1:**
[figure not shown]
Is the technology roadmap.

### 2.2. Study population. Sample recruitment

We will recruit and include 60 participants with perennial AR from the outpatient Department of Otorhinolaryngology Head and Neck Surgery Sant by the People’s Hospital of Anshun City of Guizhou Province (China). All participants receiving this service must be seen by a physician (allergy subspecialist or general physician). All those diagnosed with perennial AR (of more than 1 years duration) according to the Guidelines for AR^[1,12,13]^ during that appointment will be referred to a Outpatient physician of otolaryngology Head and neck Surgery, who will check whether they meet the other inclusion and exclusion criteria before offering them the opportunity to participate in the study.

The inclusion criteria will be: We will include participants with perennial AR only (not seasonal AR); above 18 years old to below 65 years old; both sexes; The participants has not received specific immunotherapy in the past 1 month or has not used any drugs to treatment the AR in the past 1 week; The participants must be examined with a positive result in the IgE sensitization test to aeroallergens (skin prick test or serum allergen specific IgE); they must with normal cognitive function and agree to participate in this study and sign the informed consent form.

The exclusion criteria will be: Participants who met any of the following criteria were excluded: The participants with severe nasal septum deviation, chronic rhinosinusitis, bronchial asthma, nasal polyps, upper respiratory tract infection, lung infection and other diseases; with severe dysfunction of heart, liver, kidney or autoimmune diseases; Pregnant or lactating women; Allergic constitution and allergic to the experimental drugs and ingredients; With drug addiction history; With major neuropsychiatric diseases who cannot take medication regularly; participating in other clinical trials.

The participants who meet all inclusion criteria and not meet exclusion criteria will have the opportunity to participate in the study and provide all relevant information orally and in writing. They will be told to be randomly assigned to study groups, each of which will be treated with a different drug, all of which are appropriate for their condition, and the goal of the study is to determine which drug produces the best results.

To maintain this blindness, the participants will not be told which group they had been assigned to.

If they decide to participate, they will be asked to sign an informed consent form, and the recruiting physician will conduct a baseline assessment.

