## Abstract

**Methods::**

A randomized, prospective, double-blind (patient and evaluator) clinical trial. The participants (n = 60) will be randomly distributed into 2 groups. The experimental group will receive a sublingual Immunotherapy for 3 months. The control group will receive the mometasone furoate nasal spray for 3 months. Before treatment, 1 month and 3 months after treatment, total nasal symptom score scale, Visual analogue Scale and Quality of Life questionnaire of rhinoconjunctivitis will be measured and Changes of the serums of IgE, interferon-γ, IL-4, IL-17, tumor necrosis factor-α, IL-5, IL-9, IL-13, IL-25, IL-33, vascular endothelial growth factor, TSLP and IL-22 in both groups. The measurements will be performed by the same researcher who was unaware of the participants’ subgroup.

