### 2.4. Variables studied

The recruiting physician (PhD in otolaryngology with 8 years of experience in the field) will perform all assessments for the study and remain blinded to the group to which subjects are assigned at all times.

Table 1 shows the sociodemographic variables and the values that each 1 may have. The following variables: sex, age, occupation, contact information, duration of symptoms, allergic history and Genetic history will be recorded at the beginning of treatment by anamnesis.

**Table 1 T1:** Independent sociodemographic variables.

Variable	Values
Sex	Man/Woman
Age	Years
Occupation	What kind of job
Contact information	Phone number
Duration of symptoms	Daily – Weekly – Monthly – Quarterly – Annual
Allergic history	Yes/No
Genetic history	Yes/No

Table 2 shows the outcome variables, the evaluation period for each variable, and the measurement tools used. All assessments will be performed by a physician, who will also be responsible for recruitment, and the group assigned to each subject will be assessed in a blinded manner throughout the assessment period.

**Table 2 T2:** Outcome variables, the evaluation period for each variable.

Outcome variables	Evaluation period			Measuring instrument
	Baseline	1 mo post-treatment		3 mo post-treatment
Nasal symptoms and signs score	X	X	X	TNSS
Intensity of nasal pain (main symptom)	X	X	X	VAS
Rhinitis Quality of Life Questionnaire	X	X	X	RQLQ
Serological test	X	X	X	The level of serological indicators

RQLQ = rhinoconjunctivitis quality of life questionnaire, TNSS = the total nasal symptom score, VAS = Visual analog scale.

The primary outcome indicator is the decrease in the total nasal symptom score^[14]^ (including self-assessment of nasal congestion, runny nose, itchy nose, and sneezing) and Changes in the level of serological indicators (Enzyme-linked immunosorbent assay will be used to detect). The secondary outcome indicators are visual analogue scale and Standardized Rhinoconjunctivitis Quality of Life Questionnaire^[15]^ and mitigate changes in drug use. Data will be recorded by Case report forms (CRFs) before treatment, at 1 month of treatment, and at 3 months of treatment.

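### The entry rule joins its two treatment-free conditions with 'or', so patients recently treated with AR drugs or immunotherapy can enrol and blur the baseline of both primary outcomes

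*Protocol article*

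**What the plan says.** The inclusion criteria in section 2.2 of the protocol article are separated by semicolons. One item carries both treatment-free conditions: the patient has not received "specific immunotherapy in the past 1 month or has not used any drugs to treatment the AR in the past 1 week". Its first half reads "The participants has not received specific immunotherapy in the past 1 month" and its second half "or has not used any drugs to treatment the AR in the past 1 week". The section then states how the criteria combine: "The participants who meet all inclusion criteria and not meet exclusion criteria will have the opportunity to participate in the study".

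The exclusion criteria in the same section do not mention current AR drugs or earlier immunotherapy. The nearest item is "Allergic constitution and allergic to the experimental drugs and ingredients", which concerns intolerance of the study products, not previous use. After consent, "the recruiting physician will conduct a baseline assessment"; the article describes no run-in or washout between the two.

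Section 2.4 begins its definition of the primary outcome with "The primary outcome indicator is the decrease in the total nasal symptom score" and adds the change in serological indicators. On treatment, the abstract states "The experimental group will receive a sublingual Immunotherapy for 3 months", while the control group uses mometasone furoate nasal spray for the same period.

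**The concern.** The item states two alternative ways to qualify where one would expect two requirements. The exposures it lets through are of the same kinds as the trial treatments: AR drugs, which may include nasal steroid, and specific immunotherapy.

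Both primary outcomes are measured as change from the baseline visit. A patient whose symptoms or serum markers are already altered by treatment on that day starts from a value that does not reflect untreated disease. That can make the change within each arm look smaller than it is, and it mixes treated and untreated starting points, which widens the spread of the change scores. The trial also aims to separate the immunological mechanisms of the two treatments, and recent exposure to either kind of treatment blurs the serological baseline needed for that. Patients have had perennial AR for more than a year and are recruited at a specialist outpatient clinic, so recent treatment is plausible, though its frequency is not reported.

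**Working it through.** The plan gives no figure on this point, so there is none to reproduce. The check has three steps.

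**1. What the wording admits.** Let A be no specific immunotherapy in the past month, and B be no AR drug in the past week.

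| A holds | B holds | Eligible as written (A or B) | Eligible if both required (A and B) |
|---|---|---|---|
| yes | yes | yes | yes |
| yes | no | yes | no |
| no | yes | yes | no |
| no | no | no | no |

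Three of the four patterns are eligible as written, against one if both are required. The rule that all inclusion criteria must be met does not change this, because A-or-B is a single criterion.

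**2. How many entrants this could involve.** This step is an illustration on assumed shares. Let s be the share of otherwise eligible patients with an AR drug in the past week and r the share with immunotherapy in the past month, taken as independent. Among those enrolled under the 'or' rule, the share failing at least one condition is 1 − (1 − s)(1 − r) / (1 − s·r).

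- s = 10%, r = 2%: 1 − 0.882/0.998 = 11.6%, about 7 of 60.
- s = 50%, r = 10%: 1 − 0.450/0.950 = 52.6%, about 32 of 60.

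**3. Effect on the change scores.** These inputs are also assumed. Let q be the share of entrants on an effective AR drug (20% to 40%) and m the amount by which the drug lowers baseline TNSS, in units of the SD of the change score (0.5 to 1.0). Suppose the follow-up score is not otherwise affected by the earlier drug.

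- The mean decrease within an arm falls by q·m: from 0.2 × 0.5 = 0.1 SD to 0.4 × 1.0 = 0.4 SD.
- Difference between arms: randomisation gives both arms the same expected q, so the expected shift is q·m − q·m = 0.
- The variance of change is multiplied by 1 + q(1 − q)m²: from 1 + 0.16 × 0.25 = 1.04 to 1 + 0.24 × 1.00 = 1.24.
- In terms of information, 60 patients would then count as 60/1.04 = 57.7 down to 60/1.24 = 48.4 patients with an untreated baseline.

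The recent-immunotherapy route is not covered by this calculation. Its effect depends on how many spray-arm patients had immunotherapy and how long any benefit lasts, and the documents give neither.

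**The case against.** The strongest reply is that this is a slip of wording. The article's English is uneven throughout, two treatment-free windows in one item make most sense if both apply, and the authors may well have meant 'neither … nor'. That is plausible, but it does not rescue the text. The negation is repeated on each side of 'or', which sets out alternatives, and a recruiting physician who follows the sentence literally would enrol the patients described.

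A second reply concerns the consequences, and most of it stands.

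- A reader might infer that the baseline is in fact contaminated. The wording only permits this; no rate of earlier use is reported.
- A reader might take the 0.1 to 0.4 SD shift as bias in the treatment comparison. It falls equally on both arms in expectation and cancels. Chance imbalance remains possible in a trial of 60, but that is not systematic bias.
- A reader might add that patients allocated to immunotherapy lose their earlier drug and appear to worsen. No section says that earlier drugs are stopped at entry, and section 2.4 lists change in drug use among the secondary outcomes, so this cannot be assumed.
- The case report form is not shown, so the article cannot be faulted for lacking boxes that record the two conditions. Section 2.2 already has a physician check eligibility before participation is offered.

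At the low end of the assumed range, a 4% rise in variance is trivial.

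**Conclusion.** The concern holds as a defect in an operative eligibility rule. As written, the criterion admits patients with recent AR drug use or recent immunotherapy, and nothing else in the article prevents it. The likely harm is an understated change within each arm and a noisier comparison: about 4% to 24% more variance in the change score if 20% to 40% of entrants are exposed and the drug effect is 0.5 to 1.0 SD of the change score. Those inputs are assumptions, and an analysis that adjusts for baseline could recover part of the loss.

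Systematic bias between the arms is not shown. The one route that could affect the contrast itself is lasting benefit from recent immunotherapy in patients allocated to the spray, and its size cannot be derived from the documents. The reading of the grammar is firm; the size of the consequence is not. The point does not invalidate the trial, but it should be corrected before recruitment.

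**What to change.** Reword the item in section 2.2 so that both stated conditions must hold, either by replacing 'or' with 'and' or by a 'neither … nor' construction. Leave the two stated durations as they are; their length is a clinical matter and is not questioned here. Have the physician confirm both conditions at the existing eligibility check, before baseline TNSS and the baseline blood sample are taken.

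The change costs one reworded sentence. Its downside is that a few patients become ineligible or enter later. If the authors intended 'both' all along, practice does not change.

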## 1. Introduction

Allergic rhinitis (AR) is a common and frequent ailment of otolaryngology. It is a perennial or seasonal disease with symptoms such as sneezing, runny nose, itching nose, nasal congestion and anosmia.^[1]^ Numerous epidemiological studies have been shown that AR affects 10% to 40% of the global population.^[2]^ It has become a major chronic inflammatory respiratory disease and is considered 1 of the most difficult diseases to treat globally.^[3]^

Although AR is not a serious disease, but due to its recurrent, persistent, and complicating characteristics,^[4–6]^ it has a serious impact on the quality of life and socio-economic well-being of patients and has become a major global health problem.^[7]^ It is reported that economic losses in EU countries can be between 30 and 50 billion euros per year.^[8]^ A large sample study in the United States showed that AR reduced worker productivity more than any other disease, including hypertension, diabetes, and heart disease.^[9]^

The treatment of AR mainly includes environmental control, drug therapy, immunotherapy, etc.^[9,10]^ all kinds of treatment methods have their advantages. However, there are no good measures to avoid dust mite allergy at present. Therefore, it is becoming more and more important for scholars to change patients’ allergic physique through specific immunotherapies.

AR is a noninfectious chronic inflammatory disease of the nasal mucosa mainly mediated by immunoglobulin E after exposure to allergens in atopic individuals.^[11]^ Regulating the immune balance of Th1/Th2/Th17 cells during the occurrence and development of AR is considered to be an important approach in the current treatment of AR. But there is increasing evidence that innate immune response is also the pathogenesis of AR. Innate lymphoid cells (ILCs) are involved in mucosal immune formation, lymphocyte development, tissue damage repair and epithelial barrier protection, and play an important role in fighting infection, regulating inflammation and maintaining immune homeostasis. Some studies have proposed that the 3 subsets of innate lymphocytes (ILC1s, ILC2s, ILC3s) are functionally approximately corresponding to Th1, Th2, and Th17 of T helper cells. However, current studies have not been conclusive, and the specific mechanism of ILCs in the development of AR has not been fully elucidated.

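### The sensitisation criterion is not tied to the immunotherapy's allergen, and the allergy exclusion, read literally, conflicts with it

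*Protocol article*

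**What the plan says.** The experimental arm is described in the Abstract: "The experimental group will receive a sublingual Immunotherapy for 3 months". The Introduction presents this class of treatment as allergen-specific; its aim is to "change patients’ allergic physique through specific immunotherapies". The control arm receives mometasone furoate nasal spray for the same period.

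Section 2.2 sets two relevant inclusion conditions. The first is disease type: "We will include participants with perennial AR only (not seasonal AR"). The second is sensitisation: "The participants must be examined with a positive result in the IgE sensitization test to aeroallergens", shown by either a skin prick test or serum specific IgE. Neither names an allergen or refers to the content of the extract.

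The exclusion list in the same section contains "Allergic constitution and allergic to the experimental drugs and ingredients", with no exception for the active allergen of the immunotherapy.

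The Introduction describes AR as "mainly mediated by immunoglobulin E after exposure to allergens in atopic individuals". It mentions dust mite as background ("there are no good measures to avoid dust mite allergy at present"), and the Discussion mentions it again when summarising other studies. The eligibility criteria never use it.

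**The concern.** There are two separate problems in the stated criteria.

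1. **The inclusion test is wider than the treatment.** An allergen-specific extract is expected to act through sensitisation to the allergen it contains. A positive test to any aeroallergen satisfies the criterion, so a patient sensitised only to something else can enter and be allocated to the extract. The same patient allocated to mometasone could still benefit, because the spray does not depend on which allergen is responsible. The resulting error runs in one direction, against immunotherapy. It can affect both primary outcomes named in section 2.4, the total nasal symptom score and the serum markers. Randomisation does not remove it, because it changes what the comparison estimates. Section 2.2 also tells candidates that each study treatment suits their condition, which the entry test does not secure.

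2. **The allergy exclusion collides with the inclusion.** Entry requires proof of IgE sensitisation, and the disease is described as one of atopic people. An exclusion for an allergic constitution, taken at its word, points at the same people. The recruiting physician cannot apply it consistently without knowing what it is meant to catch.

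**Working it through.** The article states no alpha, power, effect size or standard deviation, so it has no figure on this point to reproduce. The check is a comparison of the texts plus one line of algebra.

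**Inputs from the article**
- 60 participants, each with a 1/2 chance of either arm (section 2.3), so 60 × 1/2 = 30 expected per arm.
- Sensitisation to aeroallergens in general; perennial AR only (section 2.2).
- Active comparator, mometasone (Abstract).

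**Inputs not in the article**
- a: mean allergen-specific effect of immunotherapy in correctly sensitised patients.
- b: mean effect of mometasone.
- q: share of the immunotherapy arm not sensitised to the extract's allergen.

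**Size of the shift**
- All correctly sensitised: contrast = a − b.
- Share q mis-sensitised, with no allergen-specific benefit: contrast = a(1 − q) − b.
- Shift = [a(1 − q) − b] − (a − b) = −q·a.

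The shift does not depend on b. As an assumed range, q = 10% is 0.10 × 30 = 3 patients in the immunotherapy arm and a shift of 0.10a; q = 40% is 0.40 × 30 = 12 patients and a shift of 0.40a. These values only show the scale; nothing in the article supports a particular q.

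**Readings of the exclusion, set against the inclusion**
- *Allergic constitution as an exclusion in its own right, meaning atopy.* Everyone who passes the IgE test is excluded, and nobody is eligible.
- *Both conditions must hold, and the ingredients include the active allergen.* Everyone who passes the IgE test already meets the first condition, so the second decides. Patients sensitised to the extract's allergen are removed, and those sensitised only to other allergens remain.
- *Ordinary hypersensitivity to the study products or their other components.* The eligible population contains the patients the extract targets and adds others without the matching sensitisation. The reference to allergic constitution then does no work, unless it has a narrower meaning that is not given.

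The three readings admit very different populations, and the text does not choose between them. The gap in the inclusion criterion remains on the third reading, which is the most ordinary one.

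**The case against.** The strongest reply is that this is a journal article condensing a fuller protocol. The identity of the extract may be stated there, and leaving it out here is no fault. Perennial disease also narrows the plausible allergens, and patients are diagnosed under guidelines and screened by specialists, so q may be small. That stands as a limit on size. It does not remove the point: the sensitisation rule is written out and is not tied to the treatment, and the exclusion is written out and does not fit the rule beside it.

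A reader might infer that the eligible population is the reverse of the treatable one, or that every atopic patient is excluded. The article does not support either as a general statement. Each follows from one reading of the exclusion only, and they cannot both be true: if every atopic patient were excluded, there would be no mis-sensitised patients to randomise. On the ordinary reading the eligible population is too wide, not reversed.

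A reader might also infer a definite loss of power. That does not follow either. Against an active comparator the contrast moves from a − b to a − b − q·a. If immunotherapy is truly better, the difference shrinks and may change sign. If the spray is better, its advantage grows. If the two are equal, a difference in favour of the spray appears. Power could fall or rise, and any figure would need an effect size the article does not give.

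**Conclusion.** The concern holds in a limited form. As written, the inclusion criterion allows patients without the matching sensitisation to be randomised to an allergen-specific extract, and this shifts the comparison against immunotherapy by about q times the immunotherapy effect. The result assumes that such patients gain no allergen-specific benefit and that mometasone works regardless of the allergen. Neither q nor the effect size is given, so the size cannot be fixed, and it may be small because only perennial AR is admitted.

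The allergy exclusion conflicts, read literally, with the required IgE sensitisation and with the article's description of AR. This is a conflict between stated rules, not a missing detail. It is worth correcting before recruitment, though it is not shown to defeat the trial.

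**What to change.** - **Inclusion.** Require the positive skin prick or serum specific IgE result to be to the allergen contained in the study immunotherapy, and name that allergen in the criterion. The test is already part of screening. The cost is a few more screen failures, from patients sensitised only to other allergens, and so somewhat slower recruitment.
- **Exclusion.** Reconcile the allergy exclusion with the inclusion criterion. The sponsor should state whether it covers the active allergen of the extract or only other components, and what an allergic constitution is meant to exclude. The content of that rule is a clinical decision for the sponsor and investigators; the request here is that the two criteria agree. The cost is a clarification of wording.
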